## Abstract

The National Institutes of Health Stroke Scale (NIHSS) is commonly used to triage and monitor the evolution of stroke victims. Data regarding NIHSS knowledge in nurses and physicians working with stroke patients are scarce, and a progressive decline in specific knowledge regarding this challenging scale is to be expected even among NIHSS certified personnel. This protocol was designed according to the CONSORT-eHealth (Consolidated Standards of Reporting Trials) guidelines. It describes the design of a randomized controlled trial whose primary objective is to determine if nurses and physicians who work in stroke units improve their NIHSS knowledge more significantly after following a highly interactive e-learning module than after following the traditional didactic video. Univariate and multivariable linear regression will be used to analyze the primary outcome, which will be the difference between the score on a 50-question quiz answered before and immediately after following the allocated learning material. Secondary outcomes will include knowledge retention at one month, assessed using the same 50-question quiz, user satisfaction, user course duration perception, and probability of recommending the allocated learning method. The study is scheduled to begin during the first semester of 2022.

## 1. Introduction

### 1.1. Background

Stroke is a frequent and time-critical emergency associated with significant morbidity and mortality [1,2]. Even though relative stroke incidence and mortality have declined since 1990, the expansion of the global population has resulted in an overall increase in the absolute number of strokes [3]. In the context of the COVID-19 pandemic, an association between SARS-CoV-2 infection and stroke has been described, with infected patients being at higher risk of worse functional outcomes and even death [4]. Efficiently assessing stroke victims is therefore more important than ever to limit the high morbidity burden associated with this pathology. Indeed, some interventions, such as intravenous thrombolysis and thrombectomy, improve functional and survival prognosis after stroke [1]. As these treatments are more effective when performed rapidly, cerebral imagery must be promptly obtained after patient admission. Scanners and Magnetic Resonance Imaging units are, however, often overloaded and overbooked [5,6], and delays in obtaining cerebral imagery are associated with worse functional and survival outcomes [7]. Adequate and timely triage is therefore mandatory, and most guidelines recommend using the National Institutes of Health Stroke Scale (NIHSS) to triage stroke victims for revascularization treatments [5,8]. Both patients with very mild [9] and very severe stroke [10] have their particularities of presentations, causes, and outcomes. Moreover, the NIHSS is also used in many stroke units to monitor the patients’ evolution [11,12], with neurological monitoring every 6 h being mandatory in Swiss stroke units in the initial surveillance phase after stroke [13]. It is therefore critical that stroke unit personnel master the application of this scale, as interpersonal variability in its interpretation can lead to inappropriate diagnostic or therapeutic procedures [14].

Digital learning resources play an important role in education today [15]. Over the last decade, e-learning modules have become popular in health professional education [16,17]. Medical and paramedical personnel often work in shift patterns, thus greatly limiting their availability for traditional teaching sessions. E-learning modules are very helpful in this setting, as the content can be viewed without time constraints, can be interrupted and resumed as needed, and can be highly interactive. Self-paced highly interactive e-learning modules have been shown to improve user satisfaction [18,19].

Traditionally, the NIHSS has been taught using a didactic video created by Dr. P. Lyden [20], which is freely available on the internet [21]. Although usually effective in teaching medical procedures [22], videos lack interactivity, making them less engaging than interactive learning materials. However, engagement has been shown to improve knowledge acquisition [23,24].

To enhance learner engagement, we have created a highly interactive electronic learning (e-learning) module using Storyline (Articulate Global, Inc., New York, NY, USA). This module was shown to be more effective than the traditional didactic video in paramedics [18] and in medical students [19]. However, the two prior studies assessing the impact of this e-learning module were carried out in populations naïve to the use of this scale. Moreover, these studies were not designed to determine an effect on knowledge retention.

With time, nurses and physicians working in a stroke unit might have forgotten or overlooked certain key aspects of the application of the NIHSS. We hypothesize that our e-learning module might be more effective in reminding them of the principles underlying the application of the NIHSS than the traditional didactic video. We furthermore hypothesize that knowledge retention at one month should be higher after following this module.

### 1.2. Objectives

Our primary objective is to determine if healthcare workers belonging to a stroke unit improve their NIHSS knowledge more significantly after following a highly interactive e-learning module than after following the traditional didactic video.

The secondary objectives are to perform a cross-sectional description of actual NIHSS knowledge in these specific wards and to determine whether following either training material allows better retention of knowledge at one month.

## 2. Materials and Methods

### 2.1. Study Design and Setting

A prospective, multi-centric, web-based, triple-blind (participants, investigators, data analyst) randomized controlled trial will be carried out following the CONSORT-eHealth guidelines [25] and integrating elements from the Checklist for Reporting Results of Internet E-Surveys (CHERRIES) (Figure 1) [26].

### 2.2. Online Platform

An internet-based and GDPR (General Data Protection Regulation)-compliant study platform will be created using the Joomla 3.9 content management system (Open Source Matters, Inc., New York, NY, USA) [27]. Randomization will be stratified according to professional status (nurse or resident physician), prior NIHSS knowledge (limited, moderate, or extended), and institution by virtue of specific links displayed on the front page. Clicking on the appropriate link will automatically randomize the participant into one of two groups (video or e-learning) through the use of Gegabyte’s Random Article module [28]. A specific and straightforward registration form (Membership Pro, Joomdonation [29]) will then be displayed. Participants will have to enter and confirm a valid e-mail address, choose a secure password, and validate a captcha field. After clicking on the “Register” button, a generic email containing a data policy statement will be sent to the email address entered by the participant. Simultaneously, the participant will be automatically logged in and a first questionnaire will be displayed.

### 2.3. First Questionnaire

This questionnaire (Table 1) is designed to gather all relevant demographic information regarding the participant and to obtain data regarding their prior NIHSS training and knowledge. It will be administered using the Community Surveys 5.6 component (CoreJoomla) [30].

Regular expression (Regex) rules will be used to avoid invalid data entry. A 5-point Likert scale (very low/not at all to very high/very much) will be used to record appropriate data.

After completing this first questionnaire, participants will be redirected to a first 50-question quiz designed to assess their baseline knowledge. This quiz is identical to the one used in our previous studies [18,19]. After completing this quiz, participants will be shown the training material they have been allocated to.

### 2.4. Learning Material

The control group will follow the traditional didactic video created by Dr. P. Lyden [20], USA, which we have subtitled in French [31]. Meanwhile, the e-learning group will be presented with version 21c of our e-learning module [32]. This module was created using Storyline 3 (Articulate Global Inc., New York, NY, USA) and contains 184 interactive slides. Its structure follows the logic supporting the NIHSS (Figure 2).

Participants are required to go through all 12 chapters before reaching the final chapter, which summarizes the entire NIHSS score. Video extracts taken from the original didactic video have been embedded in each chapter (Figure 3), as their presence has been shown to improve knowledge acquisition [19].

In this module, quizzes and feedback [33,34] are used extensively to enhance learner engagement and promote knowledge acquisition (Figure 4). Whenever the learner gives a wrong answer, the feedback message includes the possibility to review the scoring logic related to the specific NIHSS item being tested.

Depending on the complexity of the item, specific animations or interactions are used to facilitate knowledge acquisition. This is for example the case for visual fields (Figure 5) and for extinction/inattention (Figure 6).

After completing the learning material, participants will be asked to answer the same 50-question quiz to determine their knowledge acquisition. At the end of this quiz, a post-course satisfaction questionnaire will be displayed (Table 2).

### 2.5. Knowledge Retention

One month (28 days) after completing the second 50-question quiz, participants will receive an email inviting them to test their knowledge retention. After completing this last questionnaire, they will be awarded a course completion certificate. There will be no other incentive to promote their participation.

### 2.6. Outcomes

The primary outcome will be the difference between the score on the 50-question quiz answered before and after following the allocated learning material. Secondary outcomes will be the overall performance in the pre-course 50-question quiz according to profession and prior NIHSS experience, performance in the same quiz undertaken one month after completion of the learning material (knowledge retention), time to course and quiz completion, user satisfaction with the learning method, user perception of the duration of the course, and probability that the user would recommend the learning material they have been allocated to a colleague.

### 2.7. Participants and Sample Size

Seventy-two participants are required to have 80% chance of detecting a difference of 2 points in the post-course 50-question quiz between groups at the 5% significance level. A total of 120 invitations should be sent, and a participation rate of 60% will therefore be required.

Disclaimers and data policy statements will be displayed on the front page and on the registration page (through a link that will open these statements in a modal).

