### 2.8. Data Curation and Statistical Analysis

Stata 16 (StataCorp LLC, College Station, TX, USA) will be used for data curation and statistical analysis. Data will be curated by one author [name] ([name]), who will assign neutral names randomly to the e-learning group and the video group. The curated DTA file will then be transferred to another author [name] ([name]) for data analysis.

A univariate linear regression will be used to analyze the primary outcome. Then, a multivariable linear regression model will be generated with profession, prior NIHSS knowledge, and work center as adjustment variables. The conditions of application will be checked, i.e., the residues distributions normality assessed graphically on a histogram and the homoscedasticity using the residual-versus-fitted plot function in Stata.

The analysis of the same quiz undertaken one month later (knowledge retention) will follow the same procedure as the primary outcome.

The assessment of the distribution of the other continuous variables, i.e., time for course completion and time for quiz completion, will be done graphically and using the Shapiro–Wilk test in case of doubt. Data will be described as means (95%CI) or median (Q1–Q3) depending on what is applied. Then, a Student’s unpaired t-test or the Mann–Whitney U test will be applied.

The cross-sectional assessment of the performance in the pre-course 50-question quiz will be described overall and according to profession and prior NIHSS experience.

A sensitivity analysis will be performed by excluding those who have previously followed either the e-learning module or the video from Patrick Lyden [20].

User satisfaction, user course duration perception, and probability of recommendation will be assessed using a 5-point Likert scale and analyzed graphically, then using the Fisher’s exact test.

The data file will be uploaded to the Mendeley Data repository.

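### The 80% power in section 2.7 is stated for the post-course score, but the primary test is on the pre-to-post change, so the stated power does not belong to the planned analysis

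*Protocol article*

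**What the plan says.** Section 2.7 (Participants and Sample Size) reads: "Seventy-two participants are required to have 80% chance of detecting a difference of 2 points". The variable named there is the score after the course: "detecting a difference of 2 points in the post-course 50-question quiz between groups at the 5% significance level". The section gives no SD and does not say whether the test is one- or two-sided.

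Section 2.6 (Outcomes) defines a different variable: "The primary outcome will be the difference between the score on the 50-question quiz answered before and after following the allocated learning material". The abstract agrees with section 2.6.

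Section 2.8 (Data Curation and Statistical Analysis) then states: "A univariate linear regression will be used to analyze the primary outcome". A multivariable model follows, adjusted for profession, prior NIHSS knowledge and work center. The pre-course quiz score is in neither model.

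**The concern.** With two groups and no covariates, linear regression of the change is an unpaired t-test on the change. The 80% in section 2.7 is claimed for another variable, the post-course score. A 2-point effect carries over, because randomisation makes the expected baseline scores equal. The variance does not carry over: it depends on the spread of the baseline scores and on how strongly the two scores correlate, and the protocol states neither.

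The stake is how the result will be read. If the correlation is low, a null result on the change would be taken as coming from a test with 80% power when the true figure was lower. There is little slack to absorb this: 120 invitations × 60% = 72 exactly, and section 3.2 warns that attrition may be high.

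**Working it through.** **Inputs.** From section 2.7: total N 72, power 80%, difference 2 points, significance level 5%. Assumed, because not stated: 1:1 allocation (36 per arm), a two-sided test, and no loss between the two quizzes. Unknown: the pre- and post-course SDs and their correlation ρ.

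**Step 1: the plan's own figure.** Without an SD, 72 cannot be reproduced directly, so solve for the SD that it implies:

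SD = 2 / [(1.96 + 0.8416) × √(2/36)] = 2 / (2.8016 × 0.2357) = 3.03 by the normal approximation, or 2.99 by the t-test.

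Working forwards, an SD of 3.0 gives N = 72 (normal) or 74 (t). So 72 is coherent for a post-course score with an SD of about 3.

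**Step 2: the SD of the variable tested.**

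Var(change) = SDpre² + SDpost² − 2ρ × SDpre × SDpost

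With equal SDs this is 2(1 − ρ) × SD². At ρ = 0.3, the SD of change is 2.99 × √1.4 = 3.53.

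**Step 3: power with 36 per arm.** The normal approximation is Φ(2 / (SDchange × 0.2357) − 1.96). At ρ = 0.3 this is Φ(2.40 − 1.96), about 67%; the noncentral t (70 df) gives 66%. The table uses the noncentral t. The last two columns are for the regression that includes the baseline score, with residual SD = 2.99 × √(1 − ρ²); the one extra degree of freedom it uses is ignored.

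| ρ | SD of change | Power, unadjusted change | Residual SD, baseline in model | Power, baseline in model |
|---|---|---|---|---|
| 0 | 4.22 | 51% | 2.99 | 80% |
| 0.1 | 4.01 | 55% | 2.97 | 80% |
| 0.3 | 3.53 | 66% | 2.85 | 84% |
| 0.4 | 3.27 | 72.5% | 2.74 | 86% |
| 0.5 | 2.99 | 80% | 2.59 | 90% |
| 0.7 | 2.31 | 95% | 2.13 | 98% |

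For 80% power on the unadjusted change, the total N would be about 100 at ρ = 0.3 and 86 at ρ = 0.4.

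**Step 4: unequal SDs.** The change has the same variance as the post-course score when ρ = SDpre / (2 × SDpost). That equals 0.5 only if the SDs are equal. Suppose the baseline SD were 4 (an assumption) and the post-course SD 3. The break-even ρ is then 4/6 = 0.67. At ρ = 0.5 the SD of change is √(9 + 16 − 12) = 3.61 and power is about 64%.

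**The case against.** The strongest reply is that nothing is miscalculated. The figure of 72 fits an SD of about 3, and a journal article may leave the SD and its source to a fuller document. That stands: the unstated SD is not a fault here. But a fuller document could supply an SD without reconciling section 2.7 with sections 2.6 and 2.8, which name different variables. If section 2.7 meant the change, its wording still needs correcting.

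A reader might infer that the trial is underpowered. The protocol does not support this. The same people take the identical quiz directly after the course, and their prior knowledge ranges from limited to extended, so ρ could be substantial; above the break-even value, power exceeds 80%. Equally, training could compress post-course scores and lower ρ. The direction is open.

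A reader might also argue that mixed prior knowledge inflates the SD and so cuts power. Spread that reflects stable differences between people cancels in the change score, so a larger post-course SD alone says nothing definite about the planned test.

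Nor can it be said that the SD was borrowed from unsuitable populations. The protocol notes that "the two prior studies assessing the impact of this e-learning module were carried out in populations naïve to the use of this scale", but section 2.7 does not name those studies as its source.

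Finally, the planned multivariable model adjusts for prior knowledge, profession and center, and might recover some precision. The powers above ignore that. They describe the univariate regression, which section 2.8 places first for the primary outcome.

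**Conclusion.** The mismatch is in the text and does not depend on any assumed figure: the power statement is attached to the post-course score and the primary test uses the change. The 72 participants need not give 80% power for the planned analysis.

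The size depends on quantities that the protocol does not give. With 1:1 allocation, a two-sided test and equal SDs of about 3.0, power runs from about 55% at ρ = 0.1 to 95% at ρ = 0.7, and equals 80% only at ρ = 0.5. With a wider baseline spread the break-even correlation is higher. What is established is that the 80% is unsupported for this test, not that it is too high.

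**What to change.** **Preferred.** Include the pre-course quiz score as a covariate in the primary regression. Taking the post-course score or the change as the dependent variable gives the same group effect once baseline is in the model, and this estimates the same group difference as now. Section 2.7 can then keep 72, stating the SD assumed and that the test is two-sided. The power in the right-hand column of the table holds only if the post-course SD is about 3; with an SD of 3.5 and ρ = 0 it would be about 67%. Sections 2.6 and 2.8 and the abstract need matching wording.

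**Alternative.** Keep the unadjusted change and restate section 2.7 for it, with the assumed SD of change and the power that 72 gives over a range of ρ.

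**Cost.** Short wording changes in sections 2.6, 2.7 and 2.8 and the abstract, and one covariate that is already collected. The preferred route needs no more participants if the SD of about 3 holds. The alternative may mean stating a less favourable power.

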### 3.2. Strengths and Limitations

Both pathways of the study require approximately two to four hours to be completed, and participants will be asked to repeat the 50-question quiz after one month. There is currently a high level of fatigue amongst hospital staff related to the COVID-19 pandemic [38]. Even though the personnel and the different hierarchies express a high level of enthusiasm for this type of study, uncertainty remains regarding the number of participants who will engage in this study, and attrition might be high [39]. Furthermore, even though each participant will have their own login and password, we will not have any way to ascertain that the quizzes will be completed by one person and not a group of colleagues. However, we will emphasize the single-person performance aspect of this study in the instruction page, and believe that the risk of such bias is low. Although we will specify that no external resources are allowed, we will have no way to verify that these have not been used (e.g., detailed NIHSS form or internet page with explanations). The temptation to do so can be important, especially when study subjects desire to prove that their baseline NIHSS knowledge is high. This could bias the results with an over-assessment of baseline knowledge. The heterogeneity of English and French proficiency among nurses and physicians of both hospitals could have an impact on the results of the study. The e-learning is entirely in French, and Dr. P. Lyden’s [20] original video is in English. To minimize this effect, the entire video (be it the extracts in the e-learning or the full video) has been subtitled in French. Further, participants will also be asked about their language proficiency in the initial demographic questionnaire, and the distribution assessed among groups. Finally, using a 50-question quiz to determine NIHSS knowledge cannot be considered as entirely representative of the actual clinical application of this scale. The video vignettes have, however, been validated in prior studies and should therefore represent an acceptable surrogate outcome [18,19]. Moreover, reusing the same 50-question quiz could lead to an improvement from one time to another due to a “priming effect” of the first questionnaire. However, this effect should be smoothed out given the randomization as it should occur similarly in both groups.

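### The 60% participation rate in section 2.7 is exactly 72/120 and leaves no room for loss before the second quiz, which the primary outcome needs

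*Protocol article*

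**What the plan says.** Section 2.7 of the protocol article sets the target: "Seventy-two participants are required to have 80% chance of detecting a difference of 2 points" on the post-course quiz, "at the 5% significance level". The next sentence turns that number into a recruitment requirement: "A total of 120 invitations should be sent, and a participation rate of 60% will therefore be required". No allowance for loss appears there or anywhere else in the article.

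Section 2.6 defines the primary outcome as the change in quiz score from before to after the training, so a participant contributes only after finishing both quizzes.

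Under section 2.2, clicking a link on the front page will "automatically randomize the participant into one of two groups (video or e-learning"). Registration, the first questionnaire and the first quiz follow (sections 2.2 and 2.3), then the training and the second quiz (section 2.4).

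Section 3.2 describes the burden, "Both pathways of the study require approximately two to four hours to be completed", mentions fatigue among hospital staff, and concludes that "uncertainty remains regarding the number of participants who will engage in this study, and attrition might be high".

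**The concern.** Section 2.7 sets the number who must take part equal to the number the power statement needs. These agree only if everyone who joins goes on to finish the second quiz. Section 3.2 names two separate risks, that too few people engage and that those who engage are then lost. The 60% figure deals with the first only.

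What is at stake is how the target is read during and after the trial. Seventy-two people joining would look like a met sample size, while the primary comparison would have fewer people and less than 80% power. A null result could then be taken as better supported than it is.

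**Working it through.** **Inputs from the article**
- Required number 72, power 80%, difference 2 points on the post-course quiz, 5% level, 120 invitations, 60% participation (section 2.7).
- Two groups (section 2.2).

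**Assumptions, because the article does not state them**
- Two-sided test, 1:1 allocation (36 per arm), two-sample t-test.
- SD back-solved from the article's own 72.
- Loss *a* between joining and the second quiz of 10% to 40%.

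**Step 1: reproduce the stated rate.** 72 / 120 = 0.600, and 120 × 0.60 = 72.0. The figure reproduces exactly with *a* = 0, so it contains no margin.

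**Step 2: participation needed to end with 72 completers.** Starters = 72 / (1 − *a*), rounded up; rate = starters / 120. No SD is needed.

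| Assumed loss | Starters needed | Rate out of 120 |
|---|---|---|
| 0% | 72 | 60.0% |
| 10% | 72/0.9 = 80 | 66.7% |
| 20% | 72/0.8 = 90 | 75.0% |
| 30% | 72/0.7 = 102.9, so 103 | 85.8% |
| 40% | 72/0.6 = 120 | 100.0% |

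Above 40% loss, 120 invitations cannot yield 72 completers. Equivalently, keeping 60% participation would take 134, 150, 172 or 200 invitations at 10%, 20%, 30% or 40% loss (starters / 0.6, rounded up).

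**Step 3: implied SD.** With the normal approximation, SD = 2 × √(36/2) / (1.960 + 0.842) = 8.485 / 2.802 ≈ 3.03. Solving the t-test power equation for 80% at 36 per arm gives SD ≈ 2.987. These agree closely, and the t-test value is used below.

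**Step 4: power if 60% join and some are lost.** Per-arm n = 36 × (1 − *a*); noncentrality = 2 / (2.987 × √(2/n)); power from the noncentral t distribution with 2n − 2 degrees of freedom.

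| Assumed loss | Analysable, 72 × (1 − *a*) | Per arm | Noncentrality | Power |
|---|---|---|---|---|
| 0% | 72.0 | 36.0 | 2.84 | 0.800 |
| 10% | 64.8 | 32.4 | 2.70 | 0.756 |
| 20% | 57.6 | 28.8 | 2.54 | 0.704 |
| 30% | 50.4 | 25.2 | 2.38 | 0.644 |
| 40% | 43.2 | 21.6 | 2.20 | 0.575 |

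The normal approximation with SD 3.03 gives nearly the same powers: 0.757, 0.707, 0.650 and 0.583 at 10% to 40% loss.

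**The case against.** The strongest reply is that the sentence in section 2.7 is correct as a requirement. The division is right, the text sets a condition and does not forecast recruitment, and the rate is never defined. If it means the share of invitees who supply the data the calculation needs, it already says what is asked for. This stands in part: there is no slip in the arithmetic. But nothing in the article gives the term that meaning, section 3.2 treats engaging and attrition as separate matters, and people are randomized before they take any quiz. Reading the rate as joining is the natural one, and under it there is no margin. If completion was meant, a clarifying phrase is still needed.

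A second reply is that the attrition remark may concern the one-month quiz, where loss affects only a secondary outcome. The article does not say how any loss would divide between the two stages. The same paragraph, however, opens with the length of the pathway, most of which precedes the second quiz, so loss before the primary outcome falls within the warning.

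A third reply is that the limitation is already disclosed. Disclosure in the discussion does not change the derived figure in section 2.7.

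Readers might also go further than the text allows, in three ways:
- They might infer that the authors expect heavy attrition. Section 3.2 raises it only as a possibility and gives no rate.
- They might infer that 120 is the limit of the eligible pool, so that a shortfall could not be made up. Section 2.7 says how many invitations should go out and does not rule out more.
- They might infer that power for the one-month quiz is wrongly absent. That is a secondary outcome, and an article may leave such detail to a fuller document.

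**Conclusion.** The point holds. The 60% rate delivers 72 analysable participants, and with them the stated 80% power, only if nobody is lost between joining and the second quiz. That conclusion needs only 72/120, the definition of the primary outcome and the order of the study steps.

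Its size depends on assumptions. The participation rates of 67% to 100% depend on the assumed loss alone. The powers of 0.756 to 0.575 depend also on the back-solved SD, a two-sided test and equal allocation. They refer to the 2-point post-course difference that section 2.7 powers. The primary outcome in section 2.6 is a before-to-after change, whose SD the article does not give, so these powers are illustrative and are not established values for the primary analysis.

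**What to change.** Restate section 2.7 so that 72 participants, 60% of the 120 invited, must complete both the first and the second quiz. Then state an assumed loss between joining and the second quiz, and give one of the following:
- the participation rate needed to end with 72 completers (for example 67% at 10% loss, 75% at 20%, 86% at 30%); or
- the power expected if only 60% start, with the SD, sidedness and allocation ratio behind it.

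The cost is a sentence or two and perhaps a small table. The recruitment requirement or the stated power will look less favourable. Design, outcomes and analysis are unchanged, and the restatement does not itself call for more invitations.
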